### Intervention

During the study all patients will be ventilated using PSV. In non-variable PSV, pressure support is constant breath-by-breath, and set to a target tidal volume. In variable PSV, the mean pressure support is set to achieve the same desired *V*_
*T*
_, but single values will vary randomly breath-by-breath.

### Ventilatory settings for both groups

Pressure support is to a targeted mean tidal volume of 6 to 8 ml/kg; the maximal inspiratory pressure ≤40 cmH_2_O; the flow trigger is set at 2 l/min; inspiratory cycling-off at 25% of peak flow; PEEP and FiO_2_ for oxygen saturation SaO_2_ ≥92%, with PEEP ≥5 cmH_2_O.

The adjustment of pressure support until extubation follows these rules and is equal for both therapy groups: pressure support is gradually adjusted in decrements (or increments) of 0 to 5 cmH_2_O. PEEP is decreased in steps of 0 to 5 cmH_2_O; PEEP and FiO_2_ are adjusted to achieve a SaO_2_ ≥92%, with a PEEP ≥5 cmH_2_O.

In patients ventilated with non-variable PSV, the pressure support variability is set to zero. In patients ventilated with variable PSV, the pressure support variability is as high as possible (up to 100%), while not exceeding the maximal inspiratory pressure determined by the treating physician.

The pressure support delivered by the ventilator in a given breath (P_supp_(*i*)) is determined by *P*_supp_(*i*) = Δ*P*_supp_ ± percentage-of-pressure-variability (*i*) × *P*_supp_, where the percentage-of-pressure-variability (*i*) is selected randomly from the set range and follows a Gaussian curve. Accordingly, for any given period of time each patient will receive more frequently *P*_supp_(*i*) values equivalent to Δ*P*_supp_ than extreme values of *P*_supp_(*i*).

Patients will be ventilated with the assigned mode of mechanical ventilation until extubation. In case of interruption of the assigned ventilation mode, for example during patient transport, the assigned mechanical ventilation mode has to be resumed as soon as possible.

### Extubation criteria

As the ventilator settings are reduced in a stepwise manner to reach the extubation criteria, the patient’s condition is continuously monitored. As soon as the patient fulfills the following extubation criteria for a time period of at least 30 minutes, extubation is possible:

Richmond agitation and sedation scale (RASS) ≥ −3; behavioral pain scale (BPS) ≤5 or visual analogue scale (VAS) for pain ≤3; raising hands or legs against gravity; temperature ≥36°C and ≤39°C; ability to cough to clear secretions after deflating cuff; respiratory rate 8 to 30/min; PaO_2_/FiO_2_ ≥ 200 mmHg (≥150 mmHg in patients with chronic obstructive pulmonary disease); pressure support ≤8 cmH_2_O; PEEP ≤8 cmH_2_O; systolic blood pressure 80 to 160 mmHg; heart rate 40 to 130/min and no hemodynamically relevant arrhythmia.

If extubation has occurred and the patient needs to be re-intubated within 72 hours, the extubation is defined as not successful and the assigned study mechanical ventilation mode will be reinstituted as soon as possible. Successful extubation is defined as extubation lasting 72 hours.

Non-invasive ventilation (NIV) after extubation is allowed after extubation according to local practice. However, if a PEEP level >8 cmH_2_O, or pressure support >8 cmH_2_O is required for NIV, the extubation is considered not successful.

If the patient has to receive tracheotomy during the study period, assisted mechanical ventilation will be resumed as soon as possible via the tracheal cannula according to the assigned therapy group. In tracheotomized patients successful extubation is defined as patient separation from the ventilator without reconnection for <72 h after separation. If continuous positive airway pressure (CPAP) therapy via the tracheal cannula with PEEP >8 cmH_2_O or pressure support >8 cmH_2_O is required, the separation from the mechanical ventilator is considered not successful. The study-related intervention is finished on successful extubation. Patients will be observed until ICU and hospital discharge and contacted during the follow-up period.

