### Intervention period data

During the study intervention, parameters are recorded daily at the same hour (the time of assessment is set by the local trial coordinator) within two hours of tolerance: SOFA score, ventilator mode, minute ventilation, respiratory rate, tidal volume, peak airway pressure, mean airway pressure, level of pressure support, set level of variability of pressure support, PEEP, airway inspiratory occlusion pressure at 100 ms (P0.1), FiO_2_, PaO_2_, PaCO_2_, pH, number of changes of pressure support settings, PEEP settings and FiO_2_ settings per 24 h, heart rate, mean arterial pressure, temperature, medication received in the last 24 hours (including sedatives, analgesics, neuromuscular blocking agents, corticosteroids and catecholamines) and fluid balance for the last 24 hours (including crystalloids, colloids and blood products). Selected centers will record the variation of tidal volume, pressure support, respiratory rate, inspiratory and expiratory times, as this requires additional equipment not available to all centers.

Because of logistical and organizational factors not every patient can be extubated immediately upon fulfilment of the extubation criteria (for example, at night). Therefore, the date and time of fulfillment of the extubation criteria and when extubation was performed are recorded separately. Successful extubation is documented after 72 hours of monitoring as explained before. With every extubation the intensive care delirium screening checklist score is assessed.

The need for NIV, NIV CPAP level and NIV pressure support level, as well as the total number of NIV hours, will be recorded. Incidences of tracheostomy and self-extubation will be registered.

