### Study endpoints

The primary endpoint is weaning time, defined as the time from randomization to successful extubation.

Secondary endpoints are: total time of mechanical ventilation; time from randomization to first extubation; time from randomization to fulfillment of extubation criteria; time between fulfillment of extubation criteria and extubation; ICU length of stay, in-hospital length of stay; ICU and in-hospital-mortality; mortality at day 90 and 6 months; PaO_2_/FiO_2_; PaCO_2_; total minutes of ventilation; mean tidal volume; mean pressure support; mean airway pressure; mean peak inspiratory pressure; inspiratory airway occlusion pressure at 100 ms; visual analogue scale for breathing comfort; cumulative amount of sedative and analgesic drugs; SOFA score; re-intubation rate; use of non-invasive ventilation; post-extubation duration of NIV; ventilator-free days (28 days); number of changes in mean pressure support by ICU personnel; coefficients of variation of tidal volume and pressure support; respiratory rate, and inspiratory and expiratory times.

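### As worded, the success definition for tracheotomised patients sets no 72-hour minimum, contrary to the protocol's own general definition of the primary-endpoint event

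*Protocol article*

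**What the plan says.** Study endpoints fixes the outcome: "The primary endpoint is weaning time, defined as the time from randomization to successful extubation". What counts as success is set out under Extubation criteria, in three parts.

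- **General rule.** "Successful extubation is defined as extubation lasting 72 hours". The failure side agrees with it: "If extubation has occurred and the patient needs to be re-intubated within 72 hours, the extubation is defined as not successful".
- **Tracheotomised patients.** "In tracheotomized patients successful extubation is defined as patient separation from the ventilator without reconnection for <72 h after separation".
- **Support through the cannula.** The next sentence makes the separation a failure if CPAP with PEEP above 8 cmH2O is needed, "or pressure support >8 cmH_2_O is required, the separation from the mechanical ventilator is considered not successful".

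The same section ends the study intervention at successful extubation. Intervention period data then says: "Successful extubation is documented after 72 hours of monitoring as explained before". It makes no separate provision for tracheotomised patients. It also says "Incidences of tracheostomy and self-extubation will be registered", but the article gives no expected frequency of tracheotomy.

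**The concern.** For extubated patients 72 hours is a floor: the patient must stay extubated at least that long. In the tracheotomy sentence the inequality points the other way. On its literal wording the separation need not last 72 hours, so a patient put back on the ventilator sooner could still be scored as weaned, with the clock stopped at the first short separation.

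Three things make this more than a background typo.

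- The sentence is the working definition of the primary-endpoint event for this subgroup, and the article does not restate the tracheotomy rule correctly anywhere else.
- It also decides when the study intervention ends. Daily ventilator data are collected during the intervention, so if a site acted on the literal wording, the assigned mode and those records could stop early. A later, durable separation might then be harder to date.
- The trial is open. The Discussion relies on a tightly specified protocol to limit the resulting bias and accepts that local weaning practice may affect the results. An event rule open to two readings weakens that safeguard.

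**Working it through.** **1. The 72-hour rule, side by side**

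| Place in the protocol article | Patients | Role of 72 hours |
|---|---|---|
| Extubation criteria, success | general | minimum duration |
| Extubation criteria, failure | general | re-intubation inside 72 h is failure |
| Extubation criteria, tracheotomy sentence | tracheotomised | less than 72 h, as written |
| Intervention period data | all, no exception | success documented after 72 h of monitoring |

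Three of the four statements make 72 hours a minimum. Only the tracheotomy sentence departs, so the document is inconsistent on its own terms and the odd statement can be identified.

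**2. The clause on support through the cannula**

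The tracheotomy sentence requires no reconnection. The next one names a failure condition above 8 cmH2O and is silent at or below that level. Two readings are possible.

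- *Separate failure conditions.* Any reconnection is failure, and so is support above the limit. The sentences are then compatible, but the pressure-support limit adds little, since such support already implies a ventilator.
- *Low-level support allowed.* Support at or below the limit is compatible with separation. The limit then has a function, but the readiness criteria in the same section already require pressure support and PEEP of no more than 8 cmH2O. A cannulated patient could be called separated without any change in support.

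The text does not choose between them. It expressly permits NIV after extubation, with its own limit, but gives no matching permission for the cannula. This is an unresolved ambiguity, not a contradiction.

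**3. Does the wording affect the sample size?**

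Inputs from Sample size calculation: difference 2 days, SD 5 days, so d = 2/5 = 0.4; two-tailed Wilcoxon–Mann–Whitney test; type I error 5%; power 80%; 10 dropouts per group.

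- Effective n per group, using the Wilcoxon relative efficiency for a normal parent: 104 × 3/π = 99.3.
- Noncentrality: 0.4 × √(99.3/2) = 2.82, with about 197 degrees of freedom.
- Power from the noncentral t distribution: 0.801, and 104 is the smallest n per group that reaches 0.80.
- Total: 2 × (104 + 10) = 228.

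Both stated figures reproduce. The tracheotomy definition does not enter them, so correcting it changes neither.

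**4. Illustration of dilution (assumed inputs)**

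Suppose a share g of all patients, the same in both arms, has a misclassified weaning time that carries no treatment effect. The expected difference becomes 2 × (1 − g) days and d becomes 0.4 × (1 − g). At 104 per group:

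| g | Difference (days) | Power, formula | Power, simulation |
|---|---|---|---|
| 0 | 2.00 | 0.801 | 0.805 |
| 3% | 1.94 | 0.777 | 0.777 |
| 5% | 1.90 | 0.760 | 0.760 |
| 10% | 1.80 | 0.714 | 0.716 |
| 15% | 1.70 | 0.664 | 0.662 |

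The simulation applied the Mann–Whitney test to normal data with SD 5 days, 4,000 runs per row. Of 208 evaluable patients, g = 5% is about 10 and g = 10% about 21. Only tracheotomised patients can be affected, so g cannot exceed the tracheotomy rate.

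**The case against.** The best defence is that no sensible reader would apply the sentence literally. It can be parsed, clumsily, as no reconnection at any time earlier than 72 hours after separation, which is the general rule again. The surrounding text supports that reading, and the literal one defeats the purpose of a durability criterion. This much stands: the sentence looks like a slip, and a reader should not infer that short failed separations were meant to count as weaning or were in fact counted. It does not remove the point, because the rule is misstated in the one place where it is defined for these patients.

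A reader might also infer that the cannula clause flatly contradicts the no-reconnection requirement. The documents do not support that. The clause says what fails above the limit; it does not say that support at or below the limit is success.

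Thirdly, a reader might convert the wording into a large bias. If 10% to 20% of patients were tracheotomised and the first short separation came 3 to 7 days before the durable one, an arm's mean would shorten by 0.10 × 3 = 0.3 to 0.20 × 7 = 1.4 days, or 15% to 70% of the planned 2 days. The arithmetic is right, but the article gives neither the rate nor the lead time. The result also needs the literal rule in one arm and the durable rule in the other, whereas one definition covers both arms and nothing in the article indicates uneven use. A mean shift is moreover not what the rank-based primary test measures.

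**Conclusion.** The point holds as a wrongly stated endpoint rule. The tracheotomy sentence conflicts with the general 72-hour definition in its own section and with the 72-hour documentation rule under Intervention period data. Whether low-level support through the cannula counts as reconnection is a separate, open ambiguity.

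The size of the effect cannot be derived from the documents. No tracheotomy rate is given, and tracheotomy already present at ICU admission is an exclusion criterion, so only patients tracheotomised after admission are concerned. The power figures (about 0.76 at 5% and 0.71 at 10% misclassified) rest on assumed shares, equal arms, normal data, and misclassified times that carry no treatment effect. They show what could be at stake and are not an estimate for this trial. The correction is needed because the sentence defines the primary-endpoint event and the end of the intervention in an open trial, whatever the eventual number of patients.

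**What to change.** 1. Reconcile the tracheotomy sentence with the 72-hour definition in the same section and with Intervention period data, so that one durability rule defines the event for all patients.
2. Reconcile the no-reconnection requirement with the cannula clause by stating whether support at or below the stated limit counts as reconnection. No threshold is proposed here; that choice belongs to the investigators.
3. Check any event dates already recorded for tracheotomised patients against the reconciled rule, before results by arm are seen.

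The cost is an amendment of one or two sentences and a clarification to sites. The sample size is unaffected. Step 3 should need only existing records, unless a site ended the intervention on the literal reading; the later separation date may then have to be retrieved from the clinical record.

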### Baseline data

After screening the following demographic characteristics will be documented: patient’s age, sex, height, weight, predicted body weight, date and type of hospital admission, date and type of surgery, date of ICU admission and time of mechanical ventilation. If a patient meets the inclusion and exclusion criteria we record the following: acute physiology and chronic health evaluation (APACHE) II score and sequential organ failure assessment (SOFA) score. Before and after the pre-inclusion test we record the following: date and time of pre-inclusion test, ventilation mode before and after pre-inclusion test, minute ventilation, respiratory rate, tidal volume, peak airway pressure, mean airway pressure, PEEP, FiO_2_, PaO_2_, arterial partial pressure of carbon dioxide (PaCO_2_) and pH.

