### Pre-inclusion test

Upon giving informed consent and after confirming agreement with the inclusion and exclusion criteria, a patient is monitored for spontaneous breathing activity. The transition from controlled to assisted ventilation is observed by a so-called pre-inclusion Test. After switching controlled mechanical ventilation to pressure support mode, every patient has to fulfill specific criteria for a period of one hour. This phase is to ensure that patients in both treatment groups show uniform stable spontaneous breathing activity. The time at which spontaneous breathing activity occurs will be recorded. This initial test can be interrupted and controlled mechanical ventilation resumed if the patient shows signs of hemodynamic or respiratory distress during the pre-inclusion test.

The pre-inclusion test is considered successfully passed if: temperature ≤39°C; PaO_2_/FiO2 ≥ 150 mmHg with PEEP ≤16 cmH_2_O; pH ≥ 7.30; respiratory rate ≤40/min; heart rate 40 to 130/min; systolic blood pressure >80 or <160 mmHg; a dose of noradrenaline or adrenaline <0.1 mcg/kg/min, dopamine or dobutamine <2 mcg/kg/min; no hemodynamically relevant acute cardiac arrhythmias occur.

If the patient fails the test criteria, the test will be repeated after patient recovery, at the treating physician’s discretion. Randomization only occurs after the patient passes the pre-inclusion test.

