The ViPS trial will broaden our knowledge of the impact of variable PSV on important clinical outcome variables in a mixed ICU population. The inclusion and exclusion criteria have been carefully designed to include a large number of patients, regardless of their co-morbidities, while taking safety issues into account. Thereby, the use of variable PSV, which has been evaluated only for hypoxemic lung failure, will be expanded to other patient groups. The protocol described here represents a consensus among centers and investigators with considerable experience in weaning patients from mechanical ventilation. The interventions are an agreement between several weaning strategies conducted in the participating centers, while the variable PSV settings have been carefully derived from experimental knowledge combined with clinical experience. Therefore, compliance of the participating centers to the protocol is likely.

The ViPS trial protocol has limitations that must be addressed. First, the entry criteria allow for patients with large differences in weaning duration, ranging from hours to days. These differences have been considered in the sample size calculation. Second, patients who fail to wean may be transferred to weaning centers, resulting in them being lost to follow-up and, consequently, causing a reduction in study power. Nevertheless, the dropout rates considered in the sample size calculation represent a worst case scenario for the participating centers. Third, the protocol cannot be conducted in a blinded fashion, which can favor bias. To minimize this effect, we defined a tight protocol where intervention steps mandate handling until the primary endpoint is achieved. Fourth, even though the protocol interventions represent a consensus among centers, local differences in weaning experience and standards may still affect the results of this trial. Fifth, the use of non-invasive ventilation following extubation could introduce bias in terms of a reduction of weaning time, but this effect should not affect the comparative performance of variable PSV, since it is also allowed in the control group.

In conclusion, ViPS is the first randomized controlled trial that compares variable with non-variable PSV with respect to the duration of weaning from mechanical ventilation in a mixed ICU population. This trial may also clarify how and why variable PSV improves lung functional variables, and reduces the respiratory drive.

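### P0.1 and the pressure support level are not in the list recorded at the pre-inclusion test, so two exploratory endpoints lack a baseline that would cheaply improve their precision

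*Protocol article*

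**What the plan says.** All references are to the Protocol article.

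- **Pre-inclusion test.** "After switching controlled mechanical ventilation to pressure support mode, every patient has to fulfill specific criteria for a period of one hour". Also: "Randomization only occurs after the patient passes the pre-inclusion test".
- **Baseline data.** The items recorded before and after that test include "ventilation mode before and after pre-inclusion test, minute ventilation, respiratory rate, tidal volume, peak airway pressure, mean airway pressure, PEEP", followed by inspired oxygen fraction and blood gases. The pressure support level and P0.1 are not named.
- **Intervention period data.** The daily list during the intervention repeats these ventilator and gas items and adds "level of pressure support, set level of variability of pressure support, PEEP, airway inspiratory occlusion pressure at 100 ms (P0.1".
- **Study endpoints.** Mean pressure support is a secondary endpoint, and the list goes on to "inspiratory airway occlusion pressure at 100 ms; visual analogue scale for breathing comfort".
- **Statistical analysis.** The secondary endpoints are exploratory. Independent groups are compared by Student's t-test or the Mann–Whitney test. No baseline-adjusted analysis is named for these endpoints.
- **Discussion.** The closing paragraph says: "This trial may also clarify how and why variable PSV improves lung functional variables, and reduces the respiratory drive".

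**The concern.** P0.1 and pressure support are the two variables closest to the trial's proposed mechanism. The Background argues that lower mean pressure support may lead to faster weaning, and the Discussion hopes to explain an effect on respiratory drive, which P0.1 measures.

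Both quantities exist at the end of the one-hour test, when other ventilator values are already being written down. The Randomization section has the assigned mode start immediately after allocation, and daily recording is at a fixed hour. The first listed value of either variable is therefore on treatment, up to about a day after randomization, and cannot serve as a baseline.

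Three things are at stake for these two endpoints: the precision that adjustment would bring, a check that the arms started alike, and a description of change within patients. A later analysis plan can choose an adjusted model, but it cannot supply a value that was never recorded.

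**Working it through.** **1. The plan's own figure.** The only sample size is for weaning time: difference 2 days, SD 5 days, d = 2/5 = 0.4, two-sided 5%, power 80%, Wilcoxon–Mann–Whitney test. A noncentral t calculation with the Wilcoxon efficiency 3/π (normal parent) gives 104 per group with power 0.801, and 2 × 104 + 2 × 10 = 228. This reproduces the plan. The present point does not touch it, and the plan states no power for P0.1 or pressure support.

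**2. The lists side by side.**

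| Variable | Before/after pre-inclusion test | Daily on treatment | Secondary endpoint |
|---|---|---|---|
| Tidal volume | yes | yes | yes |
| Mean airway pressure | yes | yes | yes |
| Peak airway pressure | yes | yes | yes |
| PaO2 and FiO2 | yes | yes | yes (as ratio) |
| PaCO2 | yes | yes | yes |
| Pressure support level | **no** | yes | yes (mean) |
| P0.1 | **no** | yes | yes |
| Breathing-comfort scale | no | no | yes |

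The other ventilator and gas endpoints in the table have a listed pre-randomization value. Pressure support level and P0.1 do not.

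**3. Can either be recovered from what is listed?** Peak airway pressure and PEEP are recorded after the test. If that reading is taken while the patient is still on pressure support and before the assigned mode starts, then

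pressure support ≈ peak airway pressure − PEEP.

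The article does not say this will be calculated, but the inputs are there. No listed variable can stand in for P0.1.

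**4. What adjustment is worth.** Let r be the correlation between the pre-randomization value and the endpoint value. The document gives no r, so a range is assumed. In a linear model with equal variances in the two arms:

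- share of variance left = 1 − r²
- equivalent multiple of patients = 1 / (1 − r²)
- standard error relative to the unadjusted analysis = √(1 − r²)

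| Assumed r | 1 − r² | 1 / (1 − r²) | √(1 − r²) |
|---|---|---|---|
| 0.3 | 1 − 0.09 = 0.91 | 1.10 | 0.95 |
| 0.5 | 1 − 0.25 = 0.75 | 1.33 | 0.87 |
| 0.7 | 1 − 0.49 = 0.51 | 1.96 | 0.71 |

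The endpoint may be a mean over the intervention period rather than the first on-treatment value, and pressure support is titrated and stepped down over that period. The low end of the range is therefore as plausible as the high end.

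**5. Breathing comfort.** The endpoint list runs "inspiratory airway occlusion pressure at 100 ms; visual analogue scale for breathing comfort; cumulative amount of sedative and analgesic drugs". The comfort scale appears under neither Baseline data nor Intervention period data, and Follow-up mentions only quality of life for the telephone contacts. The only other visual analogue scale is the pain scale in the extubation criteria.

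**The case against.** The strongest reply has four parts.

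- **No bias and no broken endpoint.** The endpoints are levels, not changes from baseline. They are exploratory and are compared between randomized groups. A reader might infer that without a baseline the comparison is invalid. It is not, because randomization protects it. The Discussion sentence about respiratory drive is a hope, not a stated objective. This part stands and limits the point to precision, balance and description.
- **Pressure support has a proxy.** A reader might infer that nothing is known of pressure support before randomization. Peak pressure minus PEEP approximates it, so the gain from recording it directly is smaller than the table suggests. This stands for pressure support, but not for P0.1.
- **The article condenses a fuller protocol and case report form.** Its lists are visibly incomplete. Mortality at day 90 and 6 months is an endpoint with no listed assessment under Follow-up. Heart rate and systolic pressure must be checked to pass the test, yet they are not in the list recorded around it. A reader might infer that breathing comfort will yield no data at all, but an incomplete list cannot show that. This stands and leaves the comfort scale as a minor reconciliation. It has less force for P0.1 and pressure support, where two near-identical itemised lists differ on exactly these variables.
- **Adjustment is an analysis choice.** The analysis plan is not shown and may specify it. That is fair, but adjustment needs the value to be collected.

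A reader might also infer from "the test will be repeated after patient recovery" that baseline SOFA and APACHE II can be days out of date at randomization. The text gives no interval between attempts and no expected failure rate, and it does not rule out updating the scores. That inference is not supported.

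**Conclusion.** The point holds as an inexpensive improvement to two exploratory secondary endpoints. As listed, the record at the pre-inclusion test leaves P0.1 without any pre-randomization value and pressure support with only an approximate, unplanned one. The primary endpoint and its sample size are unaffected, and the between-arm comparisons stay unbiased.

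Under assumed correlations of 0.3 to 0.7, adjustment would leave 91% to 51% of the variance, equivalent to about 1.10 to 1.96 times the patients. These figures rest on the assumed correlation, on an approximately linear relation and on the adjusted analysis actually being done. They apply chiefly to P0.1. If the full case report form already captures both values at the end of the test, only the analysis step and the published list need attention.

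**What to change.** 1. Under Baseline data, add P0.1 and the pressure support level to the values recorded at the end of the passed pre-inclusion test, before the assigned mode starts.
2. State that these two endpoints will be compared between arms with adjustment for that value, for example by a linear model with treatment and baseline, on a transformed scale if skewed. Report the baseline values by arm.
3. Where the direct pressure support reading is missing, say whether peak airway pressure minus PEEP will be used in its place.
4. As a minor point, reconcile Intervention period data with Study endpoints on the breathing-comfort scale, either by naming when it is assessed or by removing it as an endpoint.

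**Cost:** two extra readings per patient at a moment when ventilator values are already recorded, and one covariate in each of two exploratory analyses. No treatment rule changes.
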